## Abstract

**Introduction:**

The benefits of patient-reported feedback, using questionnaires that allow patients to report how they feel and function without any interpretation from healthcare professionals, are well established. However, patient-reported outcomes measures (PROMs) are not routinely collected in patients with melanoma in Australia. The aim of this study is to evaluate the feasibility and acceptability of implementing electronic PROMs (ePROMs) into routine care from the perspectives of patients with stage III melanoma and their treating clinical team.

**Methods and analysis:**

A minimum of 50 patients and 5 clinicians will be recruited to this prospective, longitudinal pilot study (ePROMs-MELanoma). The study uses a mixed-methods approach (quantitative PROMs questionnaires and end-of-study surveys with qualitative interviews) and commenced in May 2021 in surgical and medical melanoma clinics at two sites in metropolitan Sydney, Australia. The primary outcomes are measures of feasibility and acceptability, comprising descriptive questionnaire completion statistics, and proportion of patients who reported that these PROMs were easy to complete and measured items they considered important. Clinician and clinic staff views will be canvassed on the appropriateness of these PROMs for their patients, change in referral practice and uptake and incorporation into routine practice. Secondary aims include measurement of improvements in patients’ emotional and physical health and well-being, and utility of real-time data capture and clinician feedback. All participants will complete the Distress Thermometer and EQ-5D-5L questionnaires in the clinic using a tablet computer at baseline and two to three subsequent follow-up appointments. Participants who report a score of 4 or higher on the Distress Thermometer will be triaged to complete an additional three questionnaires: the QLQ-C30, Depression, Anxiety and Stress Scale and Melanoma Concerns Questionnaire-28. Results will be generated in real time; patients with psychosocial distress or poor quality of life will discuss possible referral to appropriate allied health services with their clinician. Thematic analysis of interviews will be conducted.

**Ethics and dissemination:**

Ethics approval obtained from St Vincent’s Hospital Human Research Ethics Committee on 19 September 2019 (2019/ETH10558), with amendments approved on 8 June 2022. Patient consent is obtained electronically prior to questionnaire commencement. Dissemination strategies will include publication in peer-reviewed journals and presentation at international conferences, tailored presentations for clinical societies and government bodies, organisational reporting through multidisciplinary meetings and research symposia for local clinicians and clinic staff, and more informal, lay reports and presentations for consumer melanoma representative bodies and patient participants and their families.

**Trial registration number:**

ACTRN12620001149954.

STRENGTHS AND LIMITATIONS OF THIS STUDYThis prospective, longitudinal cohort intervention pilot study, conducted at two sites, examines the perspectives of patients, clinicians and clinic staff.A stakeholder reference panel, with consumer representation, was formed in the planning stages of this study and is actively involved in oversight of the study.The study uses a triage system of distress screening to minimise survey burden for those who are not distressed and maximise information collection from those who are.Summary reports from the completed questionnaires, including the first use of the Melanoma Concerns Questionnaire-28, a bespoke melanoma patient-reported outcome measures questionnaire, are immediately forwarded to the treating clinician in real time, so they can be discussed during the patient’s consultation.Limitations include the absence of a control group and an unavoidable reduction in the participant enrolment target due to the impact of COVID-19 restrictions on recruitment.

## Introduction

Patient-reported outcome measures (PROMs) are questionnaires that allow patients to report how they feel and function without any interpretation from healthcare professionals.^1^ PROMs can be used in the management of individual patients to screen for a particular condition (such as depression) and/or to monitor patient response to an appropriate intervention (such as psychological therapy).^1^ Previous research has shown that the use of PROMs can improve clinician–patient communication. One study of women with gynaecological cancers found a PROMs questionnaire helped with discussion of symptoms not typically addressed for nearly all participants (95%, n=40) and improved patient care for 97% (n=41) of participants.^2^ Other studies have found PROMs can facilitate clinician awareness and improve patient management,^3 4^ contribute to prognostic information,^3^ potentially prolong survival outcomes in patients with advanced cancer,^5^ as well as allowing patients to play a greater role in the clinical decision making process.^1^ Currently, PROMs are not routinely collected as part of melanoma treatment in Australia.

It has long been recognised that many cancer specialists are not good at identifying cues for depression and psychological distress.^6 7^ Routine screening for distress is now recommended by theUS National Comprehensive Cancer Network^8^ and the International Psycho-Oncology Society and 68 affiliated organisations have set a standard of care involving monitoring distress as the ‘6th vital sign’.^9^ Australian guidelines support the use of electronic PROMs (ePROMs) for the timely detection of psychosocial distress, but the authors note that results of trials evaluating the efficacy of distress screening have been mixed.^9^ Effective trials used strategies that minimised staff burden and ensured effective follow-up.^9^

Previous research has demonstrated increased anxiety, depression and lower quality of life in melanoma patients.^10–12^ An Australian review of psychosocial support estimated 30% of all melanoma patients report levels of psychological distress indicative of the need for clinical intervention.^13^ Stage III melanoma patients usually have more morbid surgery, including sentinel node biopsy or lymph node dissection, which impacts significantly on their quality of life. When patients with stage III melanoma attend follow-up appointments with their treating physician, the focus is primarily on detection and treatment of recurrence of disease. There is minimal focus on assessing the patients’ quality of life or psychological health status, despite recommendations from The Cancer Institute New South Wales (NSW)^14^ and the Australian Commission on Safety and Quality in Health Care.^15^ An audit of Australian cancer services reported that ‘evidence from clinical settings suggests timely identification of distress is only effective in improving medical management and patient well-being when paired with structures supportive care referrals’.^16^

A 2022 report on melanoma in Australia^17^ noted the strong evidence that:

Access to emotional support services improves the well-being of people with cancer.The opportunity to discuss feelings with a member of the treatment team or counsellor decreases psychosocial distress.Psychoeducational programs decrease anxiety and depression.

This landmark report concluded that increased screening for supportive care services should be developed as a quality indicator of melanoma clinical care.^17^

While there has been extensive research on estimating the extent of psychosocial distress in a vast range of clinical settings, subsequent translation of that knowledge into programmes and services currently lags behind gains in the medical treatment of advanced melanoma.^18^ This gap between obtaining results from PROMs and using this information as the first step in a process to actually improve patient outcomes is an overdue and urgent area of research.

By including the collection and evaluation of ePROMs data into the routine care for patients with stage III melanoma, the treating clinician will be able to identify patients who are experiencing deterioration in quality of life or psychological distress. Once identified, these patients may then be referred to the appropriate allied health professionals (eg, psychologist, specialist nurse, physiotherapist, occupational therapist and social worker) for appropriate support.

The primary aim of this pilot study is to evaluate the feasibility and acceptability of implementing ePROMs into routine care from the perspectives of both stage III melanoma patients and their treating clinical team (ie, surgeons, dermatologists, medical oncologists, psychologists and melanoma nurses). If the pilot results demonstrate technical, administrative and logistical feasibility, as well as patient, clinician and financial acceptability, this pilot will be expanded to all melanoma clinics within Melanoma Institute Australia (MIA). This expansion will provide an opportunity to collect and analyse a greater volume of data and to potentially serve as a model for wider roll-out of ePROMs across the public and private healthcare sectors in NSW and other states and territories of Australia.

## Methods and analysis

### Patient and public involvement

A stakeholder reference panel was formed in the planning stages of this pilot study. Members of this panel included experts in the field of melanoma (various clinical and non-clinical specialties), experts in patient-reported measures research, and a small group of representatives/advocates for patients with current and previously treated melanoma. Consumer involvement is considered vital to ensure that the needs and preferences of patients were incorporated alongside the knowledge and background of treating clinicians and researchers.

This stakeholder representative panel was responsible for drafting a detailed project proposal to be funded as part of the Australian National Health and Medical Research Council Centre for Research Excellence in Melanoma. Panel tasks included: selection of the most appropriate PROMs to be included in this study, with consideration of minimising patient burden while maximising data usefulness; the content of semistructured qualitative interview schedules (for patients and clinicians); development of all patient information documents, including the Participant Information Statement and Consent Forms (PISCFs), an Expression of Interest (EoI) form and the ‘About you’ demographic patient information collection form; and clinician education resources including the development of short videos about the project and advice on discussion structure, in both electronic and written formats.

In addition to the documents, the manner of recruitment was widely discussed at these meetings, as was the creation of a comprehensive REDCap database that would receive results directly from the i-Pad custom-designed software while ensuring patient confidentiality. Consumer views also strongly influenced the plan for dissemination of results to patients, clinicians and their general practitioners.

### Study design and setting

ePROMs-MELanoma is a prospective, longitudinal intervention study incorporating mixed methods (quantitative surveys and qualitative interviews). Although there is no control group, the design incorporates before-and-after study design elements allowing for comparisons of psychosocial health and quality of life in individuals with stage III melanoma before and after the introduction of ePROMs. This study will be conducted at surgical and medical melanoma clinics at MIA and at Royal Prince Alfred Hospital (RPAH), Sydney, NSW, Australia.

### Eligibility criteria and sample size

Patients are eligible to participate if they are aged 18 or over, have received a diagnosis of Stage III melanoma at least 1 month earlier, are under the care of melanoma clinicians at MIA or RPAH, and have sufficient English and cognitive ability to comprehend study materials, provide informed consent and participate in the study. Clinicians, including surgical oncologists, medical oncologists, dermatologists and melanoma general practitioners, are eligible to participate if they are currently treating and managing patients with stage III melanoma at MIA or RPAH.

This research project has experienced substantial delays to recruitment due to research staff being unable to enter clinic sites during COVID-19. In April 2022, the decision was made to reduce the initial recruitment target of 100–50 patients, so that the trial may be completed before external funding expires (the minimum number of clinician participants is five). The target reduction is justified on the basis that this project is a non-randomised feasibility pilot study. Assuming 30% of stage III melanoma patients have levels of distress that indicate the need for clinical intervention,^13^ we would expect to identify approximately 17 patients within our sample who will be triaged for discussion of referrals to support services. This number is considered sufficient to inform a decision on whether or not to proceed to a larger-scale trial with additional sites.

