After all rounds of patient questionnaires (baseline plus 2–3 follow-up rounds per patient) have been completed, all patients, clinicians and clinic staff involved in the project will be asked to complete an electronic survey providing quantitative and open-ended assessments of their experiences with the PROMs questionnaires. In addition, approximately 20% of patients (10 patients), all study clinicians and clinic staff with major involvement in the study will be invited by the research team to participate in a short (10 min) confidential interview to expand on their survey responses. Patients will be purposively sampled to maximise response variation, based on a range of individual views and experiences as identified from their survey results. Patients who complete an interview will be offered a US$30 gift card to thank them for their time, while clinicians and clinic staff who participate in an interview will not be reimbursed. Figure 1 provides a study flow chart from the patient’s perspective and figure 2 provides the study overview from the clinician’s perspective.

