### Data analysis and statistical methods

#### Quantitative analysis

Participant demographics and characteristics will be summarised for all participants using means and SD. In addition, the consent, participation and completion rates will be analysed. Consent will be defined as agreeing to participate in the study and returning a signed consent form; participation, as completing some of the components of the study; and completion, as completing all components of the study. Specifically, the proportion of eligible participants who completed the project tasks will be assessed to determine whether the inclusion of ePROMs are acceptable for patients undergoing follow-up treatment for stage III melanoma. Descriptive statistics will be reported for QoL and other questionnaire domain scores at baseline and follow-up time points. Referral and referral uptake rates will also be calculated. The small sample size of 50 for this pilot study precludes any subgroup analysis. Linear mixed effects modelling will be used to account for repeated measures and differential time points among participants. This is similar to analysis of longitudinal data from a clinical trial where measurements at follow-up time points are missing.^27^

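### The sample-size section expects about 17 triaged patients, but its own inputs (50 patients, 30% distressed) give 15

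*Protocol article*

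**What the plan says.** The section on eligibility criteria and sample size reports that recruitment delays during COVID-19 led to a decision to "reduce the initial recruitment target of 100–50 patients", that is, from 100 to 50. The reduction is justified by the study being a non-randomised feasibility pilot. An expected count follows. The premise is "Assuming 30% of stage III melanoma patients have levels of distress that indicate the need for clinical intervention", and the result is "we would expect to identify approximately 17 patients within our sample who will be triaged for discussion of referrals to support services". The section concludes: "This number is considered sufficient to inform a decision on whether or not to proceed to a larger-scale trial with additional sites".

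The sample size of 50 appears in three other places:

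- The abstract: "A minimum of 50 patients and 5 clinicians will be recruited".
- Quantitative analysis: "The small sample size of 50 for this pilot study precludes any subgroup analysis".
- Interventions, where the interview subsample is "approximately 20% of patients (10 patients"), which implies a base of 50.

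**The concern.** The expected count is a product of two numbers given in the same paragraph, and the product does not match. A reader cannot tell whether 17 is a slip, a remnant of a different target or rate, or the result of an unstated step.

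The figure matters because the next sentence names it as the number on which a decision about a larger trial can be based. A statement of sufficiency should refer to a number that the reader can reproduce. The stake is the accuracy and traceability of the justification. The viability of the study is not in question.

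**Working it through.** **Inputs.** N = 50 (Eligibility criteria and sample size; confirmed in Quantitative analysis, and by 10/0.20 = 50 in Interventions). Rate p = 0.30 (Eligibility criteria and sample size). Stated result: approximately 17.

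**Attempt to reproduce the stated figure.** Expected count = p × N = 0.30 × 50 = 15.0. The product is a whole number, so rounding cannot explain the gap. The overstatement is (17 − 15)/15 = 13%.

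**What would give 17.**

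- Holding the rate at 30%: N = 17/0.30 = 56.7, so about 57 patients.
- Holding N at 50: p = 17/50 = 34%.
- Former target: 0.30 × 100 = 30.
- Patients recruited so far (36): 0.30 × 36 = 10.8.
- A rate of one third: 50/3 = 16.7. This rounds to 17, but the rate is not stated.
- Inflating N for 10% dropout: 0.30 × 50/0.90 = 16.7. This also rounds to 17, but no dropout rate is stated.
- Counting patients triaged at any visit: screening is repeated at each visit, so this count can exceed 15. As an illustration, assume 30% at every visit and three visits. The expected count is 15 if the same patients are distressed each time, and 50 × (1 − 0.70³) = 32.9 if visits are independent. Seventeen lies between these, but the section gives no such reasoning.

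So no stated input gives 17. Some unstated ones would.

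**How much the gap matters.** For X ~ Binomial(50, 0.30), the 2.5% and 97.5% quantiles are 9 and 22, and P(X ≥ 17) = 0.32. Sampling variation is much larger than the difference of two patients. This range describes one screening occasion.

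**Side check on the completion criterion.** The Patient perceptions section deems the study feasible and acceptable overall if 60% of approached eligible patients supply baseline data and one or more follow-up sets. The triaged count is neither numerator nor denominator of that proportion. The number approached is not given, so any precision is conditional on an assumption:

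- 50 approached, 30 completers: exact 95% CI 45% to 74%.
- 83 approached, 50 completers: exact 95% CI 49% to 71%. Here 83 comes from 50/0.60 = 83.3, the most that could be approached with 60% still met if exactly 50 are recruited and all complete.

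Neither interval changes whether 15 or 17 is used.

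**The case against.** The strongest reply is that nothing depends on the difference. The text says approximately, the abstract calls 50 a minimum, 17 is an unremarkable outcome when 15 is expected, and no rule uses either number. Repeat screening could also make 17 a fair count of patients ever triaged. Most of this stands, and it is why the point is minor. It does not make the figure reproducible: 30% of 50 needs no approximation, no larger N is given, and the section does not invoke repeat triage.

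A reader might draw stronger conclusions, which the article does not support:

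- **That halving the target rests on this number.** The article gives recruitment delays and expiring funding as the reasons for the cut, and justifies it first by the study being a non-randomised feasibility pilot. The count comes after that.
- **That the count was meant to support the 60% criterion and fails to.** The section offers it for the decision on a larger trial and claims nothing about that criterion. Nor is the criterion the whole assessment, since clinician and clinic-staff views are also components of the primary outcome.
- **That missing precision for the 60% criterion is a defect.** An article commonly leaves this to the full protocol or analysis plan, which are not shown here.
- **That the source of the 30% is misrepresented.** The Introduction says the cited review "estimated 30% of all melanoma patients report levels of psychological distress indicative of the need for clinical intervention", and the sample-size section presents the stage III figure as an assumption. The wider population is therefore already disclosed.

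**Conclusion.** The stated figure is wrong on the article's own inputs: 15, not about 17. The conclusion assumes that the count means 30% of the 50 target patients on one screening occasion, which is the only calculation the section sets out. If a cumulative count was intended, 17 may be defensible, but its basis is missing.

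Severity is minor. The difference is two patients (13%), lies well within binomial variation, and changes no part of the design. A reader might infer that 50 patients are too few, or that the decision on a larger trial is undermined. The article does not support that, because it sets no minimum number of triaged patients that 17 would meet and 15 would miss.

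**What to change.** In the section on eligibility criteria and sample size, do one of two things:

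- replace 17 with about 15 on a single screening occasion, adding the 95% binomial range of 9 to 22; or
- keep 17 and state the input that produces it, for example cumulative triage over repeat visits with the assumed rate.

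Then let the sufficiency sentence refer to the corrected figure.

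Optionally, add that the triaged count does not inform the precision of the 60% completion criterion. If a precision figure is given for that criterion, label it as conditional on an assumed number approached (for example, 95% CI 45% to 74% with 50 approached, 49% to 71% with 83).

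The cost is a sentence or two of wording. The target, procedures and analysis do not change.

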### Recruitment

Recruitment has been intermittent due to delays caused by COVID-19 (April–September 2020 and June 2021–March 2022). Recruitment commenced at MIA on 28 May 2021 and at RPAH on 5 July 2021. Recruitment was extended to medical oncology clinics at MIA in March 2022 to bolster recruitment numbers. Thirty-six patients and seven clinicians have been recruited since the study commenced in May 2021, with the study expected to be completed by June 2023.

### Patient recruitment process

A study clinician will review a list of potentially eligible patients (with stage III melanoma) obtained from the MIA Melanoma Research Database to check clinical eligibility (ie, are still under the care of MIA clinicians at either site or have not progressed to stage 4 melanoma). Updated lists will then be sent to each of the treating clinicians who will be able to remove patients they feel are not appropriate to invite to participate in the study for other reasons. The clinical nurse consultant or clinic secretary will then send the approved list of eligible patients to the project officer.

These patients will be initially contacted by the project officer prior to their scheduled clinical review appointments. The project officer will send them three documents along with a covering letter (either by email or post; posted documents will contain a stamped self-addressed envelope). The email/letter will briefly introduce the study, ask patients to read the invitation to participate and the participant information statement (PIS), and to complete and return an EoI form, which provides patients with three options to select from: willing, potentially willing or not willing to participate. If patients do not respond to the request to return the EoI, the project officer will telephone them once to check whether they have received it.

The project officer will follow up those patients who have indicated their willingness or potential willingness to participate, answer any questions and concerns they may have about the study and ask them to arrive 30 min earlier for their scheduled appointment to allow time to complete the questionnaires. The PIS contains contact numbers of the academic and clinical leads for this project so patients may contact them prior to making their decision to participate. When patients arrive at the clinic for a regular appointment, they will again be given the opportunity to discuss any questions they may have regarding their participation with the project officer who will greet them, obtain their electronic consent on the iPad and show them how to complete the questionnaires on the iPad.

Patients who were recruited with stage III melanoma but progress to stage IV disease during the study can choose whether to continue in the study or not. Any continuing stage IV patients will be asked to complete an interview at the end of the study to provide an assessment of how helpful they found this project to be considering their changing treatment and needs.

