### Patient perceptions

Patient ratings of feasibility and acceptability will be assessed in several ways. The first is by the proportion of eligible patients approached who completed baseline and at least one set of follow-up PROMs data. If 60% of patients meet this requirement, the study will be deemed feasible and acceptable overall.

Data on individual patient measures of feasibility and acceptability will also be collected. In the first set of two triage questionnaires, all questions are mandatory, but with the second set of three questionnaires, patients are not required to answer all questions. Metadata from the patients who are triaged to complete the second group of questionnaires will be collected to provide an estimate of the mean time taken to complete the PROMs questionnaires and the amount of missing data (providing a second measure of patient acceptability for those who completed all five questionnaires). If patients take more than 30 min to complete the five questionnaires, they will be considered as not having met this acceptability criteria. Additional measures will include changes in baseline and follow-up scores and the proportion of patients who: ‘agree or strongly agree’ that the PROMs were easy to complete and that the questions they completed measured issues they considered important to their QoL (online supplemental appendix 3a). Semistructured interviews with patients will also assess feasibility and acceptability through the following main question themes: enjoyment of completing the PROMs; changes in patient–clinician communication; changes in their management; and improvements or challenges they found in the processes.

10.1136/bmjopen-2022-066852.supp3Supplementary data

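### Clinicians may remove patients before anyone is approached, so the 60% feasibility rule describes clinician-selected patients and may overstate feasibility in routine care

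*Protocol article*

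**What the plan says.** The order of events is set out in the protocol article under Patient recruitment process. A study clinician checks a database list for patients who are still under care and have not progressed to stage IV. The updated lists go to the doctors in charge of each patient, described as those "who will be able to remove patients they feel are not appropriate to invite to participate in the study for other reasons". After this step a member of the clinic's nursing or secretarial team "will then send the approved list of eligible patients to the project officer". Only then does contact begin: "These patients will be initially contacted by the project officer prior to their scheduled clinical review appointments".

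Under Patient perceptions, the first patient measure is defined over those contacted: "The first is by the proportion of eligible patients approached who completed baseline and at least one set of follow-up PROMs data". The decision rule follows: "If 60% of patients meet this requirement, the study will be deemed feasible and acceptable overall".

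The Introduction gives the aim as to "evaluate the feasibility and acceptability of implementing ePROMs into routine care". The Quantitative analysis section says that "the proportion of eligible participants who completed the project tasks will be assessed"; it does not mention patients removed before invitation. The limitations listed after the abstract name the missing control group and the reduced enrolment target, not pre-selection.

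**The concern.** Removal by the treating clinician comes before approach, has no stated criteria, and lies outside the denominator of the 60% rule. A clinician who keeps patients out of the study, for whatever reason, cannot lower the rate. In routine use that reluctance would reduce how many patients are reached.

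What is at stake is how far a pass can be taken. The article foresees expansion to all clinics of the institute, and possibly to other services, if the pilot succeeds. A rate of 60% among patients whom clinicians thought suitable to invite does not show 60% among all eligible stage III patients. If patients judged unsuitable would have completed less often, the reported rate is higher than the rate for that wider group. A result close to the threshold could then pass on one denominator and fail on the other.

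**Working it through.** **The plan's own figure.** The 60% is a fixed threshold. The article gives no derivation, so there is nothing to reproduce.

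**Inputs**
- p, the completion rate among eligible patients approached. It is set to 60%, the threshold under Patient perceptions.
- r, the share of all eligible patients (approached plus discretionary removals) whom clinicians removed at discretion. The document does not give it; 10%, 20% and 30% are assumed.
- c, the rate at which removed patients would have completed had they been invited. The document does not give it; it is taken as 0, as half of p (30%), and as equal to p (60%).

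**Formula.** Rate over all eligible patients = p(1 − r) + c·r.

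| r (assumed) | c = 0 | c = 30% | c = 60% |
|---|---|---|---|
| 10% | 0.60 × 0.90 = 54% | 0.54 + 0.30 × 0.10 = 57% | 0.54 + 0.60 × 0.10 = 60% |
| 20% | 0.60 × 0.80 = 48% | 0.48 + 0.30 × 0.20 = 54% | 0.48 + 0.60 × 0.20 = 60% |
| 30% | 0.60 × 0.70 = 42% | 0.42 + 0.30 × 0.30 = 51% | 0.42 + 0.60 × 0.30 = 60% |

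The c = 0 column can be read in two ways. It is exactly what would be reported if discretionary removals were added to the denominator, since none of them completed. As a statement about how these patients would have fared if invited, it is the worst case.

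**In counts.** Suppose 60 of 100 approached patients complete. If those 100 remain after 20% discretionary removal, the wider group has 100 / 0.80 = 125 patients, and 60 / 125 = 48%.

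**Rate needed among those approached.** For the wider proportion to reach 60% with c = 0, p must be 0.60 / (1 − r): 66.7%, 75.0% or 85.7% for r = 10%, 20% or 30%.

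**Condition for overstatement.** The difference p − [p(1 − r) + c·r] equals r(p − c). It is positive only if some patients are removed and they would have completed less often than those approached.

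**The case against.** The case against has five parts.

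- **Direction.** The article does not describe who is removed. A reader might infer that they are the frailest or most distressed, that the rate is therefore certainly too high, and that the share scoring 4 or more on the Distress Thermometer is too low. None of this is documented. There is also a pull the other way: the approached denominator counts as failures people lost to research steps, such as an unreturned expression of interest, an unanswered follow-up call or declined consent, which routine care need not include. The net direction for routine care cannot be settled from the article. This stands, and is why the point says may overstate.
- **Counting.** A reader might infer that removals go unrecorded and can never be reported. The article is only silent, and a screening log is what a condensed article commonly leaves to the full protocol. A list exists before removal and another after it, so the number could be obtained by subtraction if both were kept. This stands.
- **True ineligibility.** The database check described covers care status and stage. The eligibility section also requires that patients "have sufficient English and cognitive ability to comprehend study materials". Some removals may apply that criterion, and those patients belong outside any eligible denominator. This stands and shapes the fix.
- **Other evidence.** A reader might infer that clinician reluctance is lost from the primary outcome altogether. It is not: clinician and clinic staff perceptions are separate components, the implementation table covers adoption and barriers to integration, and expansion depends on several kinds of feasibility and acceptability. This narrows the point to the 60% rule.
- **Normal practice.** A clinician check before invitation is common in research recruitment, and the denominator is openly stated. That is granted; the objection is not to the check.

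What remains is that the article itself states the denominator, the threshold and the overall conclusion drawn from them, and that conclusion reaches further than the patients counted.

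**Conclusion.** The point holds in a limited form. Discretionary removal precedes approach, so the 60% rule measures completion among clinician-selected patients and may overstate feasibility for all eligible stage III patients in routine care. The mechanism is documented; the direction and size are not. Across the assumed 10% to 30% discretionary removal, an observed 60% corresponds to anything from 42% (30% removed, none would have completed) to 60% (the removed would have completed equally often). This rests on assumed values of r and c and leaves aside losses to research steps that act in the opposite direction. It is an inexpensive improvement to what the rule can support, not an internal contradiction and not proof that a reported rate would be wrong.

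**What to change.** Keep the clinician check.

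1. Each treating clinician returns the list with the number removed and a coded reason. The codes separate failed eligibility (for example English or cognition) from clinician discretion.
2. For removals already made, recover the numbers by comparing the lists before and after removal, where both were kept.
3. Report the completion proportion over patients approached, as now, and over patients approached plus discretionary removals. Leave patients who failed eligibility out of both. State that the second proportion counts every discretionary removal as a non-completer, so it is a cautious figure.
4. Limit the overall feasibility and acceptability conclusion to clinician-selected patients unless both proportions reach 60%.

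The cost is small for future lists: a count and a code on a document already exchanged. With 36 of the target 50 patients recruited when the article was written, reasons for earlier removals will be incomplete. The sponsor must also report a second figure that is lower whenever there is any discretionary removal.
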